## Abstract

**Background:**

Chronic conditions such as diabetes and chronic obstructive pulmonary disease (COPD) are common and burdensome diseases primarily managed in primary care. Yet, evidence points to suboptimal quality of care for these conditions in primary care settings. Quality improvement collaboratives (QICs) are organized, multifaceted interventions that can be effective in improving chronic disease care processes and outcomes. In Quebec, Canada, the Institut national d’excellence en santé et en services sociaux (INESSS) has developed a large-scale QIC province-wide program called COMPAS+ that aims to improve the prevention and management of chronic diseases in primary care. This paper describes the protocol for our study, which aims to evaluate implementation and impact of COMPAS+ QICs on the prevention and management of targeted chronic diseases like diabetes and COPD.

**Methods:**

This is a mixed-methods, integrated knowledge translation study. The quantitative component involves a controlled interrupted time series involving nine large integrated health centres in the province. Study sites will receive one of two interventions: the multifaceted COMPAS+ intervention (experimental condition) or a feedback only intervention (control condition). For the qualitative component, a multiple case study approach will be used to achieve an in-depth understanding of individual, team, organizational and contextual factors influencing implementation and effectiveness of the COMPAS+ QICs.

**Discussion:**

COMPAS+ is a QI program that is unique in Canada due to its integration within the governance of the Quebec healthcare system and its capacity to reach many primary care providers and people living with chronic diseases across the province. We anticipate that this study will address several important gaps in knowledge related to large-scale QIC projects and generate strong and useful evidence (e.g., on leadership, organizational capacity, patient involvement, and implementation) having the potential to influence the design and optimisation of future QICs in Canada and internationally.

## Background

Preventing and managing chronic diseases represents a massive challenge to healthcare systems. Globally, chronic diseases figure among the most important causes of mortality and morbidity and impose a toll on individuals and populations that can last for years or decades [1]. In Canada, three in five adults over the age of 20 live with a chronic disease, while four in five adults have at least one modifiable risk factor for chronic illness [2, 3]. Two thirds of all deaths each year are caused by four major chronic diseases: cancer, cardiovascular diseases, diabetes, and chronic obstructive pulmonary disease (COPD) [3]. Such chronic diseases adversely impact the lives of millions of Canadians and represent a significant burden to the healthcare system, accounting for over one third of all direct healthcare expenditures and billions of dollars in indirect costs due to lost productivity [2–4].

There is a strong consensus in Canada and internationally that primary care has a critical role to play in the prevention and management of chronic diseases [4–9]. These services act as an important hub for comprehensive care that connects patients to other specialists and community services [10]. Recent reforms to strengthen preventive and team-based care in Canadian primary care services offer opportunities to improve outcomes for people with chronic diseases [4, 5, 11]. Yet, there is substantial evidence suggesting that the potential of primary care to effectively prevent and manage chronic conditions has not been realized and that many patients struggle to access high-quality chronic disease care [4, 5, 12–18].

In the past two decades, many strategies to improve the quality of healthcare have emerged and the evidence base for these strategies is growing rapidly [19]. Quality improvement (QI) strategies may include a range of activities and target individual patients or providers, teams, organizations, and/or broader health systems or networks [19, 20]. Previous systematic reviews have shown that QI projects may be more effective when they are multi-faceted and target multiple levels or stakeholders [21, 22]. Strategies targeting multiple levels of change have taken various forms, including quality assurance processes, service re-engineering, and disease management or clinical governance programs [19, 23–26].

One kind of multifaceted and multi-level intervention that is gaining in popularity is the quality improvement collaborative (QIC). A QIC involves multidisciplinary groups of clinicians and managers that participate in a structured process to identify best practices and change strategies, apply improvement methods, report results, and share information about ways of achieving improvement [27, 28]. Although models vary, QICs typically address a specific healthcare topic, involve multiple clinical teams from multiple sites, integrate a series of structured activities (e.g. meetings, workshops, audit and feedback, activities to promote collaboration), and encourage rapid cycle changes consistent with the Model of Improvement [19, 27]. In addition, a group of expert change agents often support participants by bringing together the scientific evidence, sharing practical knowledge and advice on best practices and QI methods, and facilitating implementation of strategies to improve care [19, 27]. A recent systematic review of 64 studies found that QICs resulted in a significant improvement in at least one primary outcome measure in 83% of studies, and in 85% of studies conducted in primary care [29]. A small group of studies included in the review additionally reported that QICs could be cost effective or lead to cost savings, and that intervention effects could be sustained 6 to 24 months after the end of the QIC.

While QICs are becoming increasingly widespread, important knowledge gaps for this strategy persist. Five systematic reviews on various aspects of QICs (e.g. effectiveness, components, determinants of success) [27–31] have pointed to numerous areas where new knowledge for this strategy is urgently needed. Wells and collaborators [29] have also noted that few papers provide enough detail to fully understand QIC interventions and that approaches vary considerably from one study to another. Most studies report using the Model for Improvement but it remains very difficult to determine with how much fidelity and intensity the model was implemented. Furthermore, many studies were uncontrolled before-after studies and lacked pre-intervention data before starting the intervention.

Currently, a large-scale QIC initiative known as COMPAS+ is being undertaken in the province of Quebec, Canada to improve the quality of chronic disease care in primary care settings. The fruit of a formal partnership between the Quebec Ministry of Health and Social Services (MSSS) and the *Institut national d’excellence en santé et en services sociaux* (INESSS), the provincial advisor on clinical excellence in health and social care, COMPAS+ is the first integrated clinical governance program to be implemented in the province. INESSS has the mandate to roll out COMPAS+ across the province, starting with a focus on two chronic conditions: diabetes and COPD. It is thus essential that a robust evaluation accompany this initiative, both to better understand the implementation processes and to assess the outcomes of the QICs and conditions necessary for their eventual scale-up to new chronic diseases and care settings.

### Development and previous evaluation of the COMPAS+ program

The QICs being investigated in the current study are based on an initial demonstration project conducted in Quebec’s Montérégie region (2008–2014) called the COMPAS (*Collective for best practices and improvement in primary care services*) program [32]. The program’s main goals were to engage primary care providers in continuous QI, improve interprofessional collaboration, and enhance the quality of care for priority chronic diseases [32]. The innovation central to COMPAS was the way in which it combined the use of population-based data to provide feedback on chronic disease performance, engaged participants in a process of critical reflection around their performance, and facilitated the development of QI action plans through a process of collaborative problem solving [32, 33]. These components were delivered as part of a half-day continuing professional development workshop for primary care teams from a same territory. COMPAS integrated notions of the Chronic Care Model [34] and Model for Improvement [35] and was guided by a well-articulated program theory of change [32, 33]. An evaluation of 10 workshops on diabetes management [33] revealed that COMPAS was effective in engaging participants and helping them recognize gaps between current practice and those outlined in clinical guidelines. QI action plans very frequently targeted improvement of interprofessional collaboration and addressed areas such as primary and secondary prevention of diabetes, screening practices, supporting patient self-management, and enhancing patients’ access to evidence-based treatments. However, only 25% of teams’ QI plans were fully implemented due to barriers such as a lack of time, local leadership, and supports for QI from their organizations.

The promising results of the COMPAS program led to its adoption in 2015 as a priority project by the Quebec’s Ministry of Health and Social Services. INESSS partnered with the research team and four health regions to develop and pilot an enhanced version of the program, called COMPAS+. In 2016 and 2017, new COMPAS+ QICs for COPD and diabetes were launched that built on the initial program components but also included new elements. Among the improvements was the extension of reflective practice workshops to a full day, the obtaining of formal institutional approval for the program from leaders in each region, and the creation of local implementation teams that now received long-term post-workshop supports from QI experts to facilitate the achievement of local QI projects. Furthermore, INESSS established patient involvement in COMPAS+ program governance and began involving local patient partners in workshops. Observations from this pilot phase of COMPAS+ suggest that participants are successfully engaging in the program and producing action plans, and that these plans have received higher levels of institutional support than seen previously. Still, many implementation processes and outcomes of the QICs have yet to be examined in depth.

### Study objectives

The overall aim of this study is to evaluate implementation and impact of COMPAS+ QICs for chronic diseases prevention and management in primary care. The specific objectives are to:
Evaluate the extent to which COMPAS+ is more effective than feedback alone in improving the quality of care offered to people with chronic diseases, notably diabetes or COPD.Evaluate the extent to which COMPAS+ supports the implementation of QI projects, the improvement of interprofessional collaboration and the integration of a culture of continuous QI in primary care.Describe variations in the implementation of the COMPAS+ intervention and document the influence of contextual factors on the effects of the intervention.

## Methods

### Conceptual frameworks

The main conceptual framework guiding this study is Brennan’s Informing Quality Improvement Research (InQuIRe) in primary care framework [36, 37]. Based on a systematic review, this comprehensive framework outlines [1] contextual factors at organization, team and individual levels that influence QI success, [2] mediating factors in the QI process, such as organizational readiness for change, [3] key elements of the QI process (QI methods, teamwork), and [4] proximal and distal outcomes of QI. The study also benefits from the program theory that was developed as part of the initial COMPAS program [32]. This program theory identifies the program activities, moderating factors, and outcomes specifically thought to underpin the COMPAS collaboratives. Finally, the study is guided by the Montreal Model of patient engagement, which describes how patients can be engaged in the organization and improvement of healthcare, along a continuum of engagement [38]. We strive to involve patients as true partners throughout all phases of COMPAS+ and its evaluation, and the primary patient partner (LH) has informed the objectives and methods of this proposal.

### Study design

The implementation and evaluation of COMPAS+ is embedded in an integrated knowledge translation (KT) approach. This means that all relevant stakeholders are involved in the decisions and the conduct of the different research phases. INESSS has already put in place several mechanisms (steering and implementation committees) to ensure that decision makers, clinicians, researchers and patient representatives are meaningfully engaged in COMPAS+ governance and every step of QIC development, implementation and evaluation, thus ensuring relevance and usefulness of results [39].

To achieve the study objectives, a mixed method convergent (concomitant) study design [40] will be used where the quantitative component of the study is a controlled interrupted time series (ITS) [41] and the qualitative component is a multiple case study [42]. Firstly, to asses whether COMPAS+ is more effective than feedback alone in improving the quality of services offered to people with a chronic healthcare condition, we will conduct an ITS – the most common evaluation approach used for large-scale QI collaboratives projects [29]. It represents an ideal choice of design in our circumstances given the iterative nature of local QI projects and the integrated healthcare organizations’ need for flexibility in the roll out of the QICs. Secondly, a convergent multiple case study [42] will allow our team to achieve a deep understanding of the implementation of COMPAS+, of the effectiveness of the QICs, and the factors influencing the implementation and effectiveness of the COMPAS+ intervention in different contexts. Case studies are an ideal approach for the in-depth examination of the dynamic contexts and complex processes involved in implementing collaboratives in real-world primary care settings [43]. The cases are each of the large integrated healthcare organizations participating in the study.

### Quantitative component: controlled interrupted time series

#### Setting, participants, randomization

Working in collaboration with INESSS, we will invite integrated health and social service centres to participate in the study. These integrated centres are responsible for ensuring accessibility, continuity, and quality across a continuum of health services (primary and specialist care) for the population in their region [44]. Integrated centres include all public healthcare organizations, such as hospitals, local community health and social services centres, long-term care facilities, and rehabilitation centres under a single governing body per territory. There are 22 integrated centres in the province of Quebec. Given that five had already piloted the COMPAS+ program, 17 integrated centres are eligible for this study. Each centre establishes service agreements with medical clinics in their region. Family Medicine Groups (FMGs) are the main model for interdisciplinary team-based primary care, with over 330 FMGs providing care to nearly 80% of the population. These FMGs work in collaboration with other health services provided in the community based on their geographical proximity.

We will identify nine integrated centres and stratify them according to the type of region and the size of the population served (e.g. rural (less than 150,000 inhabitants in the main city), semi-rural (150 to 200,000 inhabitants in the main city) or urban (more than 200,000 inhabitants in the main city)). They will be randomly assigned within strata to one of the two study groups using random assignment generator: 1) *control group* consisting of three centres receiving only a feedback intervention and 2) *experimental group* consisting of six centres receiving the COMPAS+ intervention in addition to the feedback intervention [41].

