#### Interrupted time series power calculation and analysis

The lack of estimates for some parameters required for the calculation of an ITS study sample precludes the calculation of a precise sample size. However, 36 points of observation (12 months before, 24 months after) should provide > 80% power to detect a significant effect of the intervention on primary outcome measures, assuming an effect size > 0.5 (medium effect or greater), autocorrelation > − 0.1, and a first-order autoregressive segmented regression model with both level (intercept) and trend (slope) changes expected [53]. To isolate the effect of the COMPAS+ QIC on the three quality indicators from other changes that could take place during the study period while adjusting for time, seasonal trends, and random errors, differences between the two study conditions (COMPAS+ or feedback only) will be assessed using linear mixed models for longitudinal data, where individuals’ data observed over time are nested into QICs to take account of the inter-QIC correlation. Descriptive statistics will also be generated for both study groups and all QICs.

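### Stratum sizes and the spread of the three control centres are not fixed, and the stated model nests individuals in QICs rather than in the randomised centres

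*Protocol article*

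**What the plan says.** All on allocation is in the protocol article, Setting, participants, randomization. Of 22 integrated centres, five piloted the programme, so "17 integrated centres are eligible for this study". The order of steps is: "We will identify nine integrated centres and stratify them according to the type of region and the size of the population served". The levels are given as examples, "e.g. rural (less than 150,000 inhabitants in the main city), semi-rural (150 to 200,000 inhabitants in the main city") and "urban (more than 200,000 inhabitants in the main city"). Then: "They will be randomly assigned within strata to one of the two study groups using random assignment generator". The control group is described as "consisting of three centres receiving only a feedback intervention", the experimental group as "consisting of six centres receiving the COMPAS+ intervention in addition to the feedback intervention". No number of centres per stratum, within-stratum ratio or block rule appears.

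Under Interrupted time series power calculation and analysis, the arms are compared with linear mixed models "while adjusting for time, seasonal trends, and random errors". Individuals' repeated data are nested in QICs to allow for correlation between QICs. The integrated centre is not named as a level, and no stratum term is mentioned.

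**The concern.** Two features of the stated plan do not fit together securely.

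**Allocation.** The totals are fixed at 3 and 6, randomisation is within strata, and stratum sizes are left open. If the strata are unequal, the probability of receiving COMPAS+ depends on region type. If a stratum holds one centre, it offers no within-stratum comparison. If the analysis then ignores the strata, a change after the start that is particular to one region type enters the treatment contrast. With three controls, one centre is a third of the arm.

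**Model level.** Centres are randomised, but the model carries QICs. If QICs are smaller units inside centres, outcomes in the same centre are treated as more independent than they may be, and at the very level at which treatment was assigned. The likely consequence is standard errors that are too small.

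**Working it through.** **Stated allocation.** 3 + 6 = 9 centres, ratio 6/3 = 2:1 overall. This reproduces. Exact 2:1 inside a stratum needs a stratum size divisible by three. With three non-empty strata, only 3/3/3 gives that throughout.

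**Probability of COMPAS+ by stratum, one control in each.** For a stratum of n centres it is (n − 1)/n.

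| Sizes | Probability of COMPAS+ | COMPAS+ centres by stratum (of 6) | Controls by stratum (of 3) |
|---|---|---|---|
| 3/3/3 | 0.67, 0.67, 0.67 | 2, 2, 2 | 1, 1, 1 |
| 4/3/2 | 0.75, 0.67, 0.50 | 3, 2, 1 | 1, 1, 1 |
| 5/2/2 | 0.80, 0.50, 0.50 | 4, 1, 1 | 1, 1, 1 |

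Within each row the composition of the arms is the same in every allocation, so in the last two rows the imbalance does not average out over randomisations.

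**What an unstratified contrast picks up.** Let d1, d2, d3 be the mean change after the start in each stratum without COMPAS+. For an equally weighted comparison of centre-level changes, the expected difference with no treatment effect is the sum of (share of COMPAS+ arm − share of control arm) × d:

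- 3/3/3: (1/3 − 1/3) in each stratum, so 0.
- 4/3/2: (3/6 − 1/3)d1 + (2/6 − 1/3)d2 + (1/6 − 1/3)d3 = (d1 − d3)/6.
- 5/2/2: (4/6 − 1/3)d1 + (1/6 − 1/3)d2 + (1/6 − 1/3)d3 = d1/3 − d2/6 − d3/6.

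Scoring the strata 0, 1, 2 in the order listed gives −2/6 = −0.33 and −3/6 = −0.50 of a stratum step. The score is arbitrary and depends on order: if the five-centre stratum is the middle one, the scored gap is 1/3 − 0 − 2/6 = 0, although the arms still differ in composition. The document gives no values for d, so the bias cannot be put on an outcome scale.

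**Single-centre strata.** Under 5/3/1 or 4/4/1 the one-centre stratum contains one arm only. If region type and population size are crossed into more than three strata, three controls cannot reach all of them.

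**Number of allocations.** With 3/3/3 and one control per stratum: 3 × 3 × 3 = 27. Without stratification: 9 × 8 × 7/6 = 84.

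**Nesting, sections side by side.**

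- Setting, participants, randomization: centres are randomised.
- COMPAS+ quality improvement collaboratives: each COMPAS+ centre offers workshops in three local service networks, so 6 × 3 = 18 networks.
- Feedback alone intervention: control centres receive no QI support beyond the summary sheet, hence no collaborative in which to nest their patients.
- Multiple case study data analysis: centre and QIC are listed as separate units.

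If a QIC is a local network, leaving out the centre treats three networks of one centre as independent. With a within-centre correlation r between network-level changes, the variance of a centre's mean is understated by the factor 1 + (3 − 1)r. The documents give no r. Over the whole range from 0 to 1 the factor runs from 1 to 3, and the standard error factor from 1 to √3 = 1.73.

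**Cost of stratum terms.** In a centre-level comparison, 9 − 2 = 7 degrees of freedom become 5. The 97.5% t quantile rises from 2.365 to 2.571, a ratio of 1.087 at equal residual variance. This illustrates the price; it does not describe the planned mixed model.

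**The case against.** The strongest reply is that the article never promises 2:1 in each stratum. It promises 3:6 overall, and one control per stratum delivers that under 4/3/2 or 5/2/2 as well. Nothing says the nine are chosen blind to region, and three from each stratum may be what is intended. This stands. A reader might infer that 2:1 within strata generally cannot be achieved. The document does not support that: the region mix of the 17 centres is not given, the strata are only examples, and the share of possible splits that divide evenly is not a probability under any selection the article describes.

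A reader might also infer that region type is confounded with arm. That is too strong. Centres are randomised, 3/3/3 gives no imbalance, and the 12 pre-intervention months separate stable level differences (and, with arm-specific slopes, existing linear trends) from the effect. Region-specific changes after the start remain. Where stratum ratios differ, randomisation does not remove their expected contribution unless the analysis uses the strata.

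A missing stratum covariate is, taken alone, no finding: the model is summarised in one sentence, and covariates are commonly left to an analysis plan that is not shown. The nesting differs, because the article states it. QIC might be meant loosely as the centre's whole collaborative. That would repair the COMPAS+ arm, but it leaves the control centres without a unit and conflicts with the separate listing of centre and QIC.

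**Conclusion.** The point holds in limited form, on two counts.

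First, the allocation rule does not secure stratum sizes compatible with a balanced 3:6 split. If the strata come out unequal, region type can be imbalanced between arms, and systematically so if the analysis ignores the strata. The 4/3/2 and 5/2/2 figures assume three strata, one control in each and equally weighted centres. They show what the text permits, not what will happen.

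Second, the stated model omits the randomised level. Too little uncertainty is the likely result if QICs are units within centres. Its size depends on a within-centre correlation that the document does not give.

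Both deserve correction before randomisation, because the Discussion counts random allocation of sites among the study's strengths and the remedy is cheap.

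**What to change.** - **Allocation.** Select three of the eligible centres in each of three defined strata, and randomise two to COMPAS+ and one to feedback within each. If this is not feasible, fix the stratum definitions and the constrained 3:6 allocation, including how many controls each stratum receives, before randomisation.
- **Model.** Make the integrated centre a random level in both arms, with local service network or QIC below it if wanted. Say what a QIC is and which unit control patients belong to.
- **Strata.** Let the analysis respect them, for example through stratum terms (including stratum by period, to address region-specific change) or randomisation inference restricted to the stratified allocations.

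**Cost.** Wording in two paragraphs and less freedom in choosing centres. If stratum terms are fitted, up to two between-centre degrees of freedom are lost (7 to 5 in a centre-level comparison). Confidence intervals will probably be wider, but they will reflect the level at which treatment was assigned.
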